### Outcomes

#### Primary outcomes measures

The primary outcome is the weight loss. First, differences between the pre and post measures for each treatment arm. Treatment success is defined as 5–10% of weight loss respect the initial weight. Then, significant differences in weight loss and other anthropometric measures, specified later, between the three treatment arms. Finally, the maintenance of weight loss during the follow-ups, significant differences between the three treatment arms.

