#### Randomization and blinding

Simple randomization will be applied using computer-generated random numbers [34], with a 1:1:1 allocation ratio. Simple randomization has proven to be reliable to large clinical research, generating similar numbers of subjects per group [34]. Participants will be randomly assigned to *en_línea* program, standard group therapy or control group. Randomization will be carried out by an independent researcher of the study. Therapists will not know the patient allocation until the coordinator inform them to begin the treatment. Thus, blinding will not be possible for the therapists during the intervention.

Currently, this study is in the recruitment phase. No statistical analysis have been performed at this time.

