### Statistical analysis

To estimate the sample size has been used the primary outcome, weight loss differences between baseline and post-treatment measures. The range of the effect size of the intervention will be 0.5 SD in group comparisons, alpha 5% and two-tail tests [51]. These data determine that we need at least 88 patients per group, considering an expected 31% dropout rate [52], our final choice will be *N* = 305 [53].

Analysis will be performed using STATA/IC 14.2. All data will be checked for missing values, accuracy and normality criteria. Intention to treat analysis (ITT) will be used to analyze the data, including all randomized participants. After that, per protocol analysis will be performed for participants who have completed 17 weeks follow-up. ANOVA for repeated measures, with type of intervention as independent variable and time (baseline and follow-up visits) as dependent variable, will be conducted to analyze primary and secondary outcomes.

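### The stated repeated-measures ANOVA treats baseline weight as an outcome visit and does not adjust for it; under its natural reading the test is valid, but some precision is given up

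*Protocol article*

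**What the plan says.** The Statistical analysis section names one model, a repeated-measures ANOVA with intervention as the independent variable and "time (baseline and follow-up visits) as dependent variable". It "will be conducted to analyze primary and secondary outcomes". No covariate, interaction term or visit-specific contrast is mentioned.

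Three other places bear on how the model should be read:

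- Primary outcomes measures defines the outcome as weight loss. It starts with "differences between the pre and post measures for each treatment arm" and goes on to compare weight loss between the three arms, after treatment and during follow-up.
- The sample size, in Statistical analysis, is based on "weight loss differences between baseline and post-treatment measures". The assumption is "The range of the effect size of the intervention will be 0.5 SD in group comparisons", with "alpha 5% and two-tail tests".
- Under Randomization and blinding, "Simple randomization will be applied using computer-generated random numbers", at 1:1:1. No stratification is described. The Procedure section has weight measured at the first appointment, before randomisation.

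**The concern.** Weight is the outcome and time is a factor, so calling time the dependent variable is wrong on any reading. More important, baseline becomes one of the outcome visits. The arms can differ there only by chance, so that visit carries no treatment effect.

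This has two consequences of different size:

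- **Unused precision.** Even when the analysis compares change between arms, it is less precise than one that conditions on baseline. Baseline weight is already collected, and simple allocation does nothing to balance it.
- **Ambiguity about the tested term.** Intervention is the only between-arm term the sentence names. Its main effect averages the null baseline visit with the later ones and keeps the full between-person variance of weight in its error. An analyst who reported that term would have a much weaker test than the one the trial was sized for.

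**Working it through.** **Inputs from the protocol article**

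- Effect 0.5 SD, two-sided 5% (Statistical analysis). The article does not say which SD; I take the SD of change.
- Analysable patients: 305 × 0.69 / 3 = 70 per arm, from N = 305 and 31% dropout.
- Post-baseline visits K: weeks 8 and 17 and months 1, 3, 6 and 12 give K = 6. Procedure lists the week-8 meeting only for the two active arms, so K = 5 is shown as well.

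**Assumptions not in the article:** compound symmetry with between-visit correlation ρ; the same true effect at every post-baseline visit; ρ = 0.85 to 0.95 for weight, with 0.5 as a low value. The SD of weight, σ, cancels.

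**The plan's own figure.** At 0.5 SD and two-sided 5%, a t-test needs 64 per group for 80% power and 86 for 90%. The stated 88 is close to the second (88 gives 91%), but no power is stated. Keeping 88 per group after 31% dropout would need 3 × 88 / 0.69 = 383, not 305. That is a separate matter; here it only explains why I use 70.

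**Step 1: change score at week 17.** SD of change = σ√(2(1−ρ)), so the true effect is δ = 0.5σ√(2(1−ρ)). Noncentrality is 0.5/√(2/70) = 2.96 and power is 84%, whatever ρ is.

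**Step 2: group-by-time F-test, baseline as a level.** For two arms, the noncentrality is λ = n × 0.25 × K/(K+1).

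- K = 6: λ = 70 × 0.25 × 6/7 = 15.0 on 6 and 828 df; power 84.0%.
- K = 5: λ = 70 × 0.25 × 5/6 = 14.6 on 5 and 690 df; power 85.2%.

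Again ρ drops out.

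**Step 3: week-17 weight adjusted for baseline.** The variance is (1−ρ²)σ², against 2(1−ρ)σ² for change. The ratio is (1+ρ)/2, a saving of (1−ρ)/2.

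**Step 4: group main effect with baseline averaged in.** The effect shrinks to δK/(K+1), and the between-person SD is σ√((1+Kρ)/(K+1)). For ρ = 0.90 and K = 6: δ = 0.224σ, shrunk to 0.192σ, over 0.956σ, which is 0.20 standardised.

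| ρ | Variance saved by adjustment | Change score | Baseline-adjusted | Main effect, K = 6 | Main effect, K = 5 |
|---|---|---|---|---|---|
| 0.50 | 25% | 84% | 92% | 91% | 89% |
| 0.85 | 7.5% | 84% | 86% | 31.5% | 30.0% |
| 0.90 | 5.0% | 84% | 85% | 21.8% | 20.8% |
| 0.95 | 2.5% | 84% | 84% | 12.9% | 12.4% |

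Entries in the last four columns are two-arm power with 70 per arm. The change-score and adjusted columns use week 17 alone; the main-effect columns average all visits.

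**Step 5: chance imbalance.** With 305/3 ≈ 102 per arm, the baseline difference between two arms has SD √(2/101.7) = 0.14σ. The probability that it exceeds 0.2σ in either direction is about 15%. Given a baseline difference D, the expected change-score difference shifts by −(1−ρ)D. At ρ = 0.90 and D = 0.2σ that is 0.02σ, about 9% of δ (0.02/0.224). Baseline adjustment removes this shift.

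**The case against.** The strongest reply is that the poor power figures belong to a term the protocol never says it will test. With baseline as a level of time, the usual treatment term is the interaction, which compares change between arms. The outcome is weight loss and the sample size is built on pre-to-post change, so the article points that way. This stands. A reader might infer from the sentence that the trial would usually miss a true effect of the planned size; the documents do not support that, because the main effect on average weight answers none of the stated objectives.

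It is also fair that the interaction test is a valid randomised comparison, and that choosing change over baseline adjustment is a loss of efficiency rather than an error. Chance imbalance does not bias the change comparison over repeated randomisations, although in a given trial it shifts the estimate slightly (Step 5).

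A condensed article may leave covariates and contrasts to a fuller plan, so their absence alone would not be a point. Here, however, the article does state a model: it fixes baseline as an outcome level and names the wrong dependent variable.

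Finally, a model restricted to post-baseline visits drops anyone without a later weight. With 31% dropout expected and an intention-to-treat analysis promised for everyone randomised, that is a real cost and the fix has to deal with it.

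**Conclusion.** The point holds as a modest one about precision and wording. Read as an interaction or change comparison, the stated ANOVA is valid and has about 84% to 85% power under the assumptions above. Baseline adjustment would reduce the variance of the week-17 contrast by 2.5% to 7.5% at ρ = 0.95 to 0.85, which for weight is worth at most about 2 percentage points of power. The saving reaches 25% at ρ = 0.5, which may be nearer the case for quality of life, analysed with the same model.

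The large loss, to about 13% to 31% power, would arise only if the group main effect were reported as the treatment effect, and it depends on high correlation: at ρ = 0.5 that term has about 90% power. The wording should rule that use out. All these figures rest on assumed correlations, compound symmetry and a constant effect; the article gives none of them.

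**What to change.** Rewrite the model sentence as follows:

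- Name weight as the dependent variable, with arm and visit as factors.
- Make the primary comparison the week-17 en_línea contrasts, against group therapy and against control, from a model with arm and baseline weight as covariate.
- For the longitudinal analysis, use the post-baseline visits as the repeated outcome, with arm, visit, arm-by-visit and baseline weight. State that the group main effect of an ANOVA that includes baseline is not the treatment effect.
- To keep every randomised participant in the analysis, either fit a constrained longitudinal mixed model, with baseline retained as an outcome and its mean held common across arms, or impute missing weights.
- Treat quality of life in the same way, with its own baseline score.

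The cost is a few sentences and the choice of how to handle missing weights. Baseline weight is already collected. The article reports that recruitment is under way and that nothing has been analysed, so the change can be made before outcome data are examined.

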## Discussion

The high obesity rates [1, 2] are an evidence that current interventions are not effective enough and new approaches are necessary [7–11]. Internet and new technologies have become essential tools in our daily routine [15]. An overuse of new technologies could trigger unhealthy behaviors [12–14] or an addition to these new resources. However, properly used Internet could be a powerful way to engage the patients in innovative treatments [16].

The future challenge is to get over the limitations of traditional weight control programs: poor long-term results and adherence rates [7–9]. Moreover, to design a new intervention the focus have to change from the disease to understand the people who is suffering the problem and their environment [10]. Thus, social support and personalized feedback should be relevant aspects to consider designing new obesity treatments [10–12]. High-intensity in-person treatments have accomplished the best results in primary care, but the large amount of people suffering obesity makes impossible offer this kind of interventions to all affected population [27–30].

*en_línea* is a project designed to be an alternative in primary care. The target population is people who are waiting for a treatment or who have to cover large distance to keep an appointment. This new approach try to consider all the aforementioned limitations. The intervention is based on the LEARN program [25], a tested weight control program, which includes social support as a relevant treatment area [10–12, 24]. *en_línea* is an online version with its own website and mobile application to reach as many obese people as possible at the same time. Online therapies are not only useful for that people who live far away [17–20]. This new intervention format is appropriate for patients who prefer not to share their intimate problems with a group, and for the new generations who feel comfortable using new technologies. Thus, a program focused on the person and their environment [10–14], with social support as a treatment area [10, 11], delivered by healthcare professionals providing personalized feedback [9–11], and with an online format [21], should provide better long-term and adherence results.

Finally, *en_línea* is the results of taking advantage of the daily use of new technologies and including them as health tools. Moreover, we reviewed previously successful weight control programs and we adapt their best features, trying to cover their limitations at the same time. Improving current treatment is the future. However, we must not forget that changing habits and losing weight are very difficult processes. Therefore, an evolution to a nonjudgmental and supportive society is necessary.

## Data Availability

Data sharing is not applicable to this article because as no datasets were generated or analyzed during the current study.

## Abbreviations

BITE: Bulimic Investigatory Test Edinburgh
BMI: Body Mass Index
CSI: Coping Inventory Strategies
DASS: Depression Anxiety Stress Scale
DEBQ: Dutch Eating Behavior Questionnaire
LEARN: Lifestyle, Exercise, Attitudes, Relationships and Nutrition.
NEQ: Night Eating Questionnaire
P-Weight: Process of Change for Weight Management
RCT: Randomized Controlled Trial
SF-36: SF-36 Health Survey
S-Weight: Stages of Change for Weight Management
TCI-R: Temperament and Character Inventory Revised
WHO: World Health Organization
